*Population of cases C-matched general population controls (D)* For each case C, two women will be selected from the general population in the HSCIC database at Exeter who, are registered in the same NHAIS system as the case at the case’s date of index diagnosis, are alive at case’s date of index diagnosis, and were born within 1 month either side of the case’s date of birth. For subsequent phases of this evaluation (main phase onwards), they will not have been included as population controls B, E, or D in previous evaluation periods, although they may be included as controls B or E within the same evaluation period.

Incident cases (C) and matched general population controls (D) will be selected *a posteriori* by the PRU, using tumour information, to suit the purpose of each case-study (see Figure 1).

**For CC3a**, incident cases (C) will be restricted to those women with invasive breast cancer, and matched general population controls (D) will be restricted to those women who have never had invasive primary breast cancer, but may have had in situ primary breast cancer prior to *and including* the case’s date of index diagnosis.

**For CC3b**, all incident cases (C) will be selected. For in situ cases, matched general population controls (D) will be restricted to those women who never had primary breast cancer (in situ or invasive) prior to *and including* the case’s date of index diagnosis; for invasive cases, to those women who never had invasive primary breast cancer, but may have had in situ primary breast cancer.

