**For CC4**, incident cases (C) will be restricted to those women with advanced stage (defined below) primary breast cancer, and matched general population controls (D) will be restricted to those women who have never had advanced stage primary breast cancer, but may have had in situ or early stage primary breast cancer prior to *and including* the case’s date of index diagnosis. Breast cancer will be defined as “advanced stage” if tumour size is larger than 20 mm, or if at least one regional lymph node is affected, or if both, and as “early stage” if tumour size is equal to or smaller than 20 mm and no regional lymph node is affected. For the purpose of data collection, we have used an inclusive definition of “advanced stage”, but we will also analyse the data by Stage to assess the association between screening and metastatic breast cancer for instance, and using only those cases which are node positive, as this is generally accepted as an important prognostic factor and as a predictor of the effect of screening on mortality (Smith et al., 2004 [10]).

If no matched control is found for a particular case (A or C) with a date of birth within 1 month either side of the case’s date of birth, the range will be expanded to 3 months either side (or 6 months either side if the case’s age at index diagnosis of primary breast cancer is under 50 or over 70).

All cases and controls will appear on the HSCIC database at Exeter. We will aim to select female cases and controls who have been registered with the NHS by age 47 (determined by either date of first registration on local NHAIS system or prior cervical/bowel screening history), and have had available data on both breast and cervical (for women aged 47–64), and, possibly bowel (for women aged 60–69) screening strictly prior to their date of first diagnosis/pseudo-diagnosis (that is, they have been invited to screening at least once), although this may not be practicably feasible for dead cases and matching controls with older age at death. Patient breast, cervical, and bowel (for the main phase) screening history, primary breast tumours attributes and treatment data will be retrieved for all cases and controls, as well as deprivation quintile.

A detailed description of the algorithm to be used for the selection of cases and controls is available from the authors.

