	**(all primary breast tumours)**	
Patient unique ID	Tumour unique ID	NHS registration by age 47
NHS number	Tumour status (in situ or invasive)	Screening office/centre
Gender	ICD10 code	Episode date
Case or Control	Date of tumour diagnosis	Screen / Test date
Date of birth	Tumour detection mode	Screen / Test outcome
Patient status (alive or dead at end of study period)	Treatment	
Cause of death – Breast cancer (where applicable)	Tumour size	
Date of death (where applicable)	Number of lymph nodes	
Age at death (where applicable)	Stage	
Date of tumour diagnosis / pseudo-diagnosis	Grade	
Age at tumour diagnosis / pseudo-diagnosis		
Cancer registry		
Geographical area		
IMD (Postcode-based)		

Information retrieved regarding living area on which to match cases and controls will vary depending on the study (pilot or main phase) and time of evaluation. NHAIS information will be obtained from HSCIC for Health for all cases and controls used for CC-1, CC-3a/b and CC-4 studies, while CN information will be used by KIT London to match cases and controls for CC-2.

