### Statistical methods

All case–control study analyses will be conducted using conditional logistic regression. Matching factors (i.e. age, area) are controlled for in the design. All statistical analyses will be performed using the statistical software STATA or R.

**CC1.** The *primary objective* of this case–control will be to assess the effect of various measures of attendance at breast screening *strictly prior to* the case’s date of first diagnosis/ the control’s date of pseudo-diagnosis on mortality from primary breast cancer. The primary measure of attendance to screening will be whether a woman ever attended at least one screen episode (indicator variable). Secondary measures will be:

• the total number of screens (counts);

• the time since last screen (continuous variable), and whether that time span fell within the past three years (≤ 3 years or > 3 years), as this corresponds to the NHSBSP protocol and approximates the estimated PCDP;

• the time since penultimate screen (continuous or categorical);

• the interval between last screen and penultimate screen (continuous or categorical);

• the maximum interval between 2 screens (continuous or categorical);

• the average interval between 2 screens (continuous or categorical);

• the patient’s age at first screen (continuous or categorical);

• the patient’s age at last screen.

*Ascertainment, self-selection* and *exposure opportunity* biases will be addressed using the methods described in the *Bias & Effect modification* section.

**
*Secondary objectives*
** will consider time since last screen stratified by age at diagnosis/pseudo-diagnosis, by first tumour detection mode, and by region (Main phase only).

The effect of attending a screen in a particular 3-year age band in the main phase (such as 47–49 inclusive), or 5-year age band in the pilot phase, on mortality from primary breast cancer in the subsequent 5-year age band (such as 50–54) will also be investigated, as performed for the cervical screening audit (Sasieni et al., 2009 [22]). The results of this analysis should be very similar to those obtained from the analysis of “time since last screen” after stratifying the analysis by age at diagnosis/pseudo-diagnosis.

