**CC2.** The *primary objective* of this case–control will be to estimate the proportional effects of screening attendance *strictly prior to* date of diagnosis/pseudo-diagnosis and cancer treatment, on prognosis in patients diagnosed with primary breast cancer. The primary and secondary measures of attendance to screening will be as for CC1; in addition, they will include tumour detection mode to assess the relationship between detection mode and choice of cancer treatment.

The regression analysis will be adjusted for tumour attributes such as stage of disease at diagnosis and other pathological features. Because of the extreme collinearity between cancer treatment and pathology variables, e.g. lymph node positivity, a major determinant of treatment choice, estimating relative effects from the regression analysis often gives unreliable/biased estimates of cancer treatment (Wishart et al., 2010 [23]). To address this statistical issue, a counterfactual analysis will be performed (Höfler et al., 2005 [24]). The treatment that an individual actually does not receive is called counterfactual treatment, and the outcome under this treatment, after treatment assignment, is referred to as counterfactual outcome. In our study, the cancer treatment effects will be constrained to the absolute effect estimated from meta-analyses of the RCTs.

*Self-selection*, *lead-time, and length* biases will be addressed using the methods described in the *Bias & Effect modification* section. Because in CC2, both cases and controls have had primary breast cancer, *exposure opportunity* bias can be assumed to be minimal.

**
*Secondary objectives*
** will consider time since last screen stratified by epoch of diagnosis to further explore collinearity among the explanatory variables.

**CC3a/b.** The *primary objectives* of these case-controls will be to estimate the effect attendance at breast screening strictly prior to date of diagnosis/pseudo-diagnosis on incidence of invasive (CC3a) or, of in situ and invasive (CC3b) primary breast cancer, and to estimate rates of overdiagnosis due to screening.

The primary and secondary measures of attendance to screening will be as for CC1, in particular time since last screen; in addition, they will include the patient’s age at last screen, and whether a woman ever missed attendance at recall assessment(s). This last measure should help assess potential room for improvement in the management of suspicious screening results.

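### The added CC3a/b exposure, ever having missed a recall assessment, mixes the effect of a suspicious screen with the effect of missing the assessment

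*Protocol article*

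**What the plan says.** Statistical methods, CC3a/b, takes over the attendance measures of CC1 and adds two, one of which is "whether a woman ever missed attendance at recall assessment(s". It also gives the purpose: "This last measure should help assess potential room for improvement in the management of suspicious screening results".

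The rest of the article fixes the setting in which this exposure would be analysed:

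- **Controls** (Participants, population D): "For each case C, two women will be selected from the general population in the HSCIC database at Exeter". They are matched to the case on date of birth and NHAIS registration area.
- **Later restriction of cases and controls** (same section): done "using tumour information, to suit the purpose of each case-study".
- **Screening-related eligibility** (same section): an aim to have screening data before diagnosis or pseudo-diagnosis, "that is, they have been invited to screening at least once".
- **Model** (Statistical methods): "All case–control study analyses will be conducted using conditional logistic regression", and "Matching factors (i.e. age, area) are controlled for in the design".
- **Data** (Variables, Table 1): the screening columns include "Screen / Test outcome".

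None of these passages restricts to, matches on or adjusts for having been recalled.

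**The concern.** A missed recall assessment is possible only after a suspicious screen. The question behind the stated purpose therefore arises only among recalled women: of those recalled, do the ones who miss the assessment fare differently from the ones who attend?

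A yes/no indicator over all CC3 women answers a different question. Its *no* group contains women who never attended screening, women screened but never recalled, and recalled women who attended every assessment. Women with a suspicious screen can be expected to have a higher incidence of breast cancer than other women, whatever happens at the assessment step. That excess sits entirely in the exposed group and only in part in the reference group.

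At stake is an inference about programme management. An odds ratio above 1 could be read as harm from missed assessments when some or all of it comes from the suspicious finding itself.

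**Working it through.** The article gives no figure for this exposure, so there is nothing to reproduce. The check is structural, followed by a rare-disease approximation with assumed inputs.

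**Inputs.** From the article: the wording of the exposure, general-population controls, matching on age and area only, and pilot numbers of at least 1400 cases C and 2800 controls D (Study size / Power calculation). Assumed, because the article does not give them: the recall share, the share of recalled women who miss assessment, and the relative incidence in recalled women.

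**Step 1: odds ratio when missing has no effect.** Let k be the incidence in recalled women relative to never-recalled women, and s the share of the reference group ever recalled. The exposed group has relative incidence k and the reference group 1 + (k − 1)s, so

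OR = k / [1 + (k − 1)s].

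| k | s = 0.08 | s = 0.16 |
|---|---|---|
| 2 | 2/1.08 = 1.85 | 2/1.16 = 1.72 |
| 4 | 4/1.24 = 3.23 | 4/1.48 = 2.70 |

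The range is 1.72 to 3.23, where the answer to the intended question is 1.

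**Step 2: fuller form and wider assumptions.** Let r be the share of all women ever recalled, m the share of recalled women who missed an assessment, and θ the true effect of missing among recalled women. Then

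OR = kθ(1 − rm) / [r(1 − m)k + (1 − r)].

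For r = 0.15, m = 0.05, k = 3 and θ = 1: 3 × 0.9925 / (0.4275 + 0.85) = 2.33. Step 1 gives the same value with s = r(1 − m)/(1 − rm) = 0.1425/0.9925 = 0.144.

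With r from 5 to 30%, m from 1 to 5% and θ = 1:

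| k | OR |
|---|---|
| 1 | 1.00 |
| 1.5 | 1.31–1.47 |
| 2 | 1.54–1.91 |
| 3 | 1.88–2.74 |
| 5 | 2.28–4.20 |

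Only k = 1 removes the distortion, and that would mean that a suspicious mammogram does not predict cancer. A real effect is distorted too: θ = 2 with r = 0.15 and k = 3 appears as 4.62 to 4.66.

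**Step 3: the contrast among recalled women.** Relative to never-recalled women, those recalled who attended have incidence k and those who missed have kθ. Their ratio is θ, and k cancels. This holds by construction. It shows that the recall component drops out, not that the contrast is free of other bias.

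**Step 4: numbers available.** Expected exposed controls in the pilot are 2800 × r × m, from 2800 × 0.05 × 0.01 = 1.4 to 2800 × 0.30 × 0.05 = 42.

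**The case against.** The strongest reply is that the article names a measure and nothing more. It states no coding and no reference group, and a fuller plan could restrict the comparison to recalled women. Several other measures in the same list, such as the interval between the last two screens, are defined only for some women, and no denominator is given for those either. The stated purpose points to women with suspicious results.

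It is true that the reference group is not named. The parallel with the other measures is weaker. An interval between screens cannot be computed for a woman with fewer than two, so the analyst must restrict or add a category. *Ever missed* can be filled in as *no* for every woman, and its wording resembles the all-women indicator for ever attending. Where the authors wanted levels for participation in the other screening programmes, they wrote them out (Self-selection bias). The biases addressed for CC3 are self-selection, exposure opportunity and lead time; none of the methods given for them deals with recall status.

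Three further objections stand:

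- The size rests wholly on assumed inputs and largely returns the assumed relative incidence, somewhat diluted.
- Missed versus attended is not a clean contrast on an incidence outcome. Attending the assessment is how a screen-detected cancer comes to be diagnosed, so attenders with cancer become cases sooner.
- Restricting the data to recalled women would break many matched sets.

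A reader might go further and infer that the measure captures recall instead of missed assessment, or that it can say nothing about management. The documents do not support this. The odds ratio is driven by both k and θ, and the protocol claims only that the measure should help. Nor can it be said from the documents that the reference group is mostly never recalled: that needs an ever-recalled share below about one half, and no recall rate is given.

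**Conclusion.** The point holds as a matter of definition. On the wording given, the exposure does not isolate the management of suspicious results, because its odds ratio would lie above 1 with no effect of missing assessment whenever recalled women have higher incidence. The direction needs only that assumption. The size does need assumed figures: about 1.7 to 3.2 for a relative incidence of 2 to 4 and 8 to 16% of the reference group ever recalled, or 1.3 to 4.2 over the wider ranges. The calculation gives the same incidence to never-screened and to screened, never-recalled women.

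It does not follow that the study will report spurious harm. The observed value also depends on any true effect of missing, on delayed diagnosis in women who miss assessment, and on how the diagnostic episode is counted.

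The importance is minor. This is one measure added to a list. The primary attendance measure and the overdiagnosis estimate, which is built on age-stratified excess and deficit in risk, do not depend on it.

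**What to change.** Define the exposure in four levels: never screened; screened and never recalled; recalled and attended all assessments; recalled and missed at least one. Enter it for all women in the conditional logistic model, so that every matched set is kept, and take missed versus attended as a contrast between two of its levels. Base the statement about managing suspicious results on that contrast and not on missed versus everyone else.

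Add two sentences. The first should state how the assessment that leads to the index diagnosis is counted, given that exposure is taken strictly before diagnosis or pseudo-diagnosis. The second should say that the contrast is to be read with caution because attending assessment advances diagnosis.

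The cost is recoding. Table 1 already requests the screen or test outcome, so this looks feasible, subject to checking that attendance at assessment can be derived from it. The downside is precision: few women are likely to miss an assessment, and on the assumptions above the pilot would hold roughly 1 to 42 exposed controls, so a usable estimate may have to wait for the main phase.

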## Discussion

This protocol aims to evaluate the policy of mammography screening as delivered in the current NHSBSP in terms of, benefits on mortality from and on incidence of invasive primary breast cancer, and, harms from overdiagnosis. In the post-RCT epoch, analytical observational studies are the design of choice. The attraction of the case–control evaluation strategy resides in that, (1) it directly relates the clinical endpoint to the screening history at an individual level, (2) being retrospective in design it requires no further follow-up and is therefore quick to perform, and finally, (3) it needs a relatively small number of cases and corresponding controls. In addition, the case–control design allows the assessment of what actually happened in the population during service screening, taking into account natural variation. It also has the flexibility to question aspects of the screening regime which were not possible to address using RCT data. The case–control design is potentially prone to a number of biases, in particular some that could confer a bias in favour of screening. However, with careful design and analysis, one can minimize the risk of biased results. The case–control design proved indeed to be a powerful tool in the evaluation of the NHS Cervical Screening Programme, informing policy on screening intervals and age ranges (Sasieni et al., 2009 [22]).

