## Background

Breast cancer is the most commonly diagnosed cancer among women in the UK, accounting for a third of all female cancer cases, and the second most common cause of cancer death: in England in 2010, the age-standardised rate per 100,000 women-years was 125.7 for incidence and 24.3 for mortality; in addition, in situ breast cancer, that is Ductal Carcinoma In Situ (DCIS) and Lobular Carcinoma In Situ (LCIS), was diagnosed at a rate of 18 per 100,000 women in 2010 (CRUK, Accessed 28 March 2013 [1]).

In the early nineties, meta-analyses of the randomised controlled trials (RCTs) confirmed the efficacy of mammographic screening for reducing primary breast cancer mortality, and led to the implementation of breast screening programmes in several regions of Europe. One of the most mature and comprehensive of those is the English National Breast Screening Programme (NHSBSP) which has been in place in England since 1988. A major issue to be addressed by the Department of Health’s (England) Policy Research Unit in Cancer Awareness, Screening and Early Diagnosis (PRU), is to evaluate the policy of mammography screening as delivered in the current NHSBSP in terms of benefits on mortality from and on incidence of invasive primary breast cancer, and harms from the most adverse outcome of breast screening. Overdiagnosis is the detection of a breast cancer that would never have been clinically identified in the lifetime of the woman if she had not been screened. In the post-RCT epoch, analytical observational studies are the design of choice.

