With time since last screen, one might expect an observed increase in incidence (excess risk) immediately after a screen (the screen-detected cases), followed by an observed decrease in incidence (deficit in risk) due to the removal of pre-clinical cases by the screen. The deficit would be expected to be attenuated with time since the screen. The analysis will be stratified by age at diagnosis/pseudo-diagnosis. Indeed, one might expect an excess risk of disease in screened ages (within screening age range) and a deficit in risk in non-screened ages (above screening age range); a potential deficit in risk may also be seen at later ages within the screening age range (i.e. at age 65–69 after up to 15 years of screening). In the absence of overdiagnosis, the initial excess risk from screening would be fully compensated by a deficit in risk over time in the absence of screening (“compensatory drop”, Puliti et al., 2011 [16]). The excess risk in screened ages and the deficit in risk in non-screened ages will be quantified and combined with National Incidence Rates to construct risk scores (Field et al., 2005 [25]) in an attempt to estimate lifetime effect of screening on incidence and overdiagnosis. As the NHSBSP has been running for at least 20 years, there should be sufficient follow-up data after screening stopped (age 70), and the method of “compensatory drop” should achieve full adjustment for lead-time (Puliti et al., 2011 [16]). If the pilot phase of the study highlights little or no follow-up after last screen, lead-time bias will be adjusted using the “postponement of screen-detected cases” method (described in the *Bias & Effect modification* section).

The estimations will be performed for all disease (in situ and invasive) and for invasive disease only.

*Self-selection* and *exposure opportunity* biases will be also addressed using the methods described in the *Bias & Effect modification* section.

**
*Secondary objectives*
** will consider time since last screen stratified by region (Main phase only).

**CC4.** The *primary objective* of this case–control will be to estimate the effect of attendance to breast screening *strictly prior to* date of diagnosis/pseudo-diagnosis on incidence of advanced stage primary breast cancer. The primary and secondary measures of attendance to screening will be as for CC1; in addition, they will include age at last screen.

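### The compensatory-drop rule does not give overdiagnosis when applied to invasive disease alone: it gives overdiagnosed minus prevented invasive cancers

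*Protocol article*

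**What the plan says.** The Discussion of the protocol article names the outcomes to be evaluated as "benefits on mortality from and on incidence of invasive primary breast cancer, and, harms from overdiagnosis". The Background defines the harm: "Overdiagnosis is the detection of a breast cancer that would never have been clinically identified in the lifetime of the woman", had she not been screened.

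Under Statistical methods, CC3a/b, the excess risk at screened ages and the deficit at older ages are to be quantified and combined with national incidence rates "in an attempt to estimate lifetime effect of screening on incidence and overdiagnosis". The reference for no overdiagnosis is that "the initial excess risk from screening would be fully compensated by a deficit in risk over time in the absence of screening". The deficit after a screen is explained as "due to the removal of pre-clinical cases by the screen". The section then adds: "The estimations will be performed for all disease (in situ and invasive) and for invasive disease only".

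Under Participants: selection of cases & controls, the invasive cases of CC3b take controls who have never had invasive breast cancer but may have had in situ disease. CC3a uses the same definition. A screened woman whose in situ lesion was removed therefore remains eligible as a screened control in the invasive analysis.

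**The concern.** The compensatory-drop rule works only if every cancer that screening brings forward is counted in the excess, so that its later absence is matched. An all-disease count meets that condition and an invasive-only count does not. If a screen finds an in situ lesion that would have become invasive, the screen-time diagnosis is not an invasive case, so it adds nothing to the invasive excess. The invasive cancer that no longer appears years later does add to the invasive deficit. The deficit can then exceed the excess with no overdiagnosis at all, and real overdiagnosis of invasive cancers can be hidden.

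At stake is the reading of one of the two planned overdiagnosis figures. The error runs towards understating the harm, and it can produce a negative value that is uninterpretable as overdiagnosis. The same number understates prevention if it is read purely as a benefit on invasive incidence.

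**Working it through.** The protocol gives no overdiagnosis result to reproduce, and it defers power calculations for CC3a, CC3b and CC4 to the pilot. The check is therefore an accounting identity, followed by two illustrations.

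**1. Identity.** Compare a screened cohort with the same cohort unscreened, over a lifetime. Let:
- L = invasive cancers whose diagnosis is brought forward
- O = overdiagnosed invasive cancers
- P = invasive cancers prevented because in situ disease was found and removed
- Q = overdiagnosed in situ lesions

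| Count | Excess | Deficit | Net |
|---|---|---|---|
| Invasive only | L + O | L + P | O - P |
| All disease | L + O + P + Q | L + P | O + Q |

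The all-disease net is total overdiagnosis, because each progressive in situ lesion enters once in the excess and once in the deficit. The invasive-only net equals invasive overdiagnosis only if P = 0. Bringing forward the diagnosis of a cancer that is already invasive does not change lifetime invasive incidence. Any lifetime reduction in invasive incidence from screening therefore requires P > 0.

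**2. Assumed counts per 1,000 expected invasive cancers.** L = 150 and Q = 0; L cancels.

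| O | P | Invasive-only net | All-disease net | True overdiagnosis |
|---|---|---|---|---|
| 50 | 0 | 5.0% | 5.0% | 5.0% |
| 50 | 30 | 2.0% | 5.0% | 5.0% |
| 50 | 50 | 0.0% | 5.0% | 5.0% |
| 50 | 80 | -3.0% | 5.0% | 5.0% |
| 0 | 30 | -3.0% | 0.0% | 0.0% |

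Worked case: O = 50 and P = 30 give excess 200, deficit 180, net 20, and 20/1,000 = 2.0%.

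**3. Rough scale, illustrative only.** The Background gives an incidence rate of 125.7 per 100,000 women-years, treated here as invasive, and states that in situ disease "was diagnosed at a rate of 18 per 100,000 women in 2010". The ratio is 18/125.7 = 14.3%. Let f be the fraction of in situ diagnoses that each prevent one later invasive cancer. The documents give no value for f. The invasive-only figure is then the true value minus 14.3% x f. The true values tried are the ends of the 3.3% to 10% range that the Background cites.

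| f (assumed) | True 3.3% becomes | True 10% becomes |
|---|---|---|
| 0.10 | 1.9% | 8.6% |
| 0.25 | -0.3% | 6.4% |
| 0.50 | -3.9% | 2.8% |

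The figure reaches zero at f = 3.3/14.3 = 0.23 and f = 10/14.3 = 0.70 respectively.

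**4. Do the planned corrections help?** The Length bias section makes robust estimation conditional on accounting for self-selection and lead time. Neither separates P from O. The fallback for short follow-up, postponing screen-detected cases, re-dates diagnoses that were made. It cannot restore invasive cancers that never occurred.

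**The case against.** The strongest reply is that the sound estimate is already in the plan. CC3b is the study labelled for overdiagnosis, and it takes in situ and invasive cases together. CC3a is labelled for incidence. The sentence on performing the estimations for invasive disease only refers back to a lifetime effect on incidence as well as overdiagnosis, so it can be read as the CC3a incidence effect. The protocol never uses a term for overdiagnosis of invasive disease alone. This limits the point to one of two planned figures but does not remove it. As written, the sentence covers both quantities, the null rule is stated without restriction, and no caveat is attached to the invasive-only result.

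Four stronger readings are tempting, and the documents do not support them:
- **That the overdiagnosis result as a whole is biased this way.** The all-disease estimate is not affected by this mechanism. The index tumour may be a first or a subsequent one, so CC3b is not a pure count of first diagnoses. That is a separate matter, which the accounting above does not test.
- **That the Discussion contradicts itself by calling invasive incidence a benefit.** It lists outcomes to evaluate, and the CC3a/b text expects an excess before a deficit. No net benefit is presumed.
- **That overdiagnosed invasive cancers are deducted twice in the benefit-harm summary.** That would follow only if the CC3a net effect were set as a benefit against all-disease overdiagnosis. The closing paragraph of Statistical methods describes projections and a prevented fraction, and does not state that subtraction.
- **That the bias has a known size.** The fraction f is assumed. The in situ rate is not stated to be age-standardised, as the 125.7 is. The 3.3% to 10% range refers to ages 50 to 79 and is not stated to be for invasive disease only.

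**Conclusion.** The point holds in a confined form. Used as an overdiagnosis estimate, the invasive-only compensatory-drop balance is O - P. It is biased downwards whenever removing in situ disease prevents any invasive cancer, and it falls below zero when P exceeds O. The direction follows from the identity and needs only P > 0. That mechanism is not spelled out in the protocol. The size cannot be derived from the documents, and the percentages above show only that modest progression fractions could matter against the range the Background cites. The point is worth correcting before analysis because the text fixes a rule that does not apply to one of the two counts it names, and the planned bias corrections do not repair it.

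**What to change.** - State under CC3a/b that overdiagnosis is estimated by compensatory drop from the all-disease (in situ plus invasive) CC3b analysis.
- Report the invasive-only lifetime result as the net effect of screening on invasive incidence, meaning overdiagnosed minus prevented invasive cancers, and do not call it overdiagnosis.
- If an invasive overdiagnosis figure is wanted, add the prevented cancers back over a stated range of in situ progression fractions, declare those fractions as assumptions, and present the result as a sensitivity range.
- Keep CC3a in the benefit-harm summary, since the effect on incidence is a stated aim, and label it there as a net effect.

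The cost is a few sentences and, if the range is wanted, one sensitivity calculation on data already to be collected. The downside is that a single invasive-only overdiagnosis figure is replaced by a relabelled result or a range.
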